## Background

The management of postoperative pain in cardiothoracic surgery remains a critical challenge, as inadequate analgesia more than doubles the risk of postoperative complications (OR 2.56), including respiratory dysfunction and prolonged hospitalization [1]. Furthermore, while opioids represent the analgesic cornerstone, their dose-dependent administration induces adverse events in approximately 20% of patients, precipitating significant morbidity such as respiratory depression, emesis, and long-term dependence [2].

This proposed protocol addresses the clinical need for innovative, non-pharmacological adjuncts to multimodal analgesia. Grounded in the limited capacity theory of attention, highly immersive distractors exhaust finite cognitive resources, modulating shared cortical networks [3] and triggering neurochemical responses, such as endorphin release, to effectively reduce perceived pain intensity [4].

Virtual Reality (VR) provides a superior level of immersion compared to traditional distraction methods, yielding up to an 88% decrease in postoperative pain [5]. Therefore, this study is designed as a proof-of-concept efficacy trial to standardize VR application in the Intensive Care Unit (ICU) setting, targeting patients (16–40 years old) undergoing cardiothoracic surgery. Our primary objective is to evaluate the preliminary clinical efficacy of this multi-session VR protocol on cumulative opioid consumption and pain intensity. It distinguishes itself by evaluating two digital strategies—active gaming, associated with the attenuation of cortical pain-related amplitudes [6], and passive 360° video contemplation—to determine their respective impact on postoperative recovery.

By establishing this early-stage framework, this protocol provides researchers and clinicians with a reproducible model for integrating digital health technology into the perioperative period, emphasizing technical feasibility, equipment hygiene, and patient safety, while gathering preliminary efficacy signals to guide future definitive trials.

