## Study design and randomization

The VR-USP study follows a Prospective Randomized Open, Blinded Endpoint (PROBE) three-arm clinical trial design with a 1:1:1 allocation ratio. The trial protocol was reviewed and approved by the Institutional Review Board (Protocol Number: CAAE 74,181,523.0.0000.0068) and prospectively registered in a primary clinical trial registry (Registry Number: NCT07063394). To evaluate the intervention’s robustness within a diverse cardiothoracic population, a block randomization sequence, consisting of twenty fixed blocks of three, is generated by an independent statistician utilizing Microsoft Excel software. This pragmatic approach is selected to reflect real-world clinical heterogeneity, ensuring that the trial’s findings maintain high external validity for routine intensive care workflows. Allocation concealment is ensured through the use of sequentially numbered, opaque, and tamper-evident sealed envelopes, numbered from 1 to 60. These envelopes are stored in a locked cabinet controlled by an independent clinical nurse who has no contact with the trial participants. Furthermore, the specific envelope for each participant is only released to the research team after a designated investigator obtains the appropriate consent documents, including parental consent and minor assent for patients under 18 years of age, and enrolls the patient. Consequently, the recruiters remain blinded to the allocation sequence prior to inclusion, and the assigned intervention arm is revealed only post-enrollment, thereby maintaining appropriate allocation concealment.

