## Sample size and study population

The fundamental rationale relies on the limited capacity theory of attention, positing that highly immersive multisensory environments exhaust finite cognitive resources to mitigate acute pain perception [7]. Furthermore, as demonstrated by Lier et al., virtual reality yields significant overall analgesic efficacy (SMD = −0.65), with particularly robust effects observed among younger demographics [8]. Consequently, the trial enrollment focuses on 60 patients aged 16 to 40 years. Eligible procedures include cardiac and specific thoracic surgeries, such as pulmonary decortication, video-assisted thoracoscopic surgery (VATS), lung biopsy, and Nuss bar pectus excavatum repair.

As this trial is designed as an early-stage, proof-of-concept efficacy study in the specific context of cardiac surgery, a formal a priori power calculation for clinical efficacy is not performed. Instead, a pragmatic sample size of 20 patients per arm (total N = 60) is established. This sample size is aligned with phase IIa / proof-of-concept trials aimed at detecting large clinical effect sizes, evaluating the safety profile of the intervention, and providing initial estimates of variance (mean and standard deviation) to adequately power future, large-scale definitive multicenter trials.

While previous studies have demonstrated substantial effect sizes for VR analgesia in other surgical contexts, extrapolating those parameters to a three-arm, highly invasive cardiothoracic population is not methodologically sound for an a priori power calculation. Therefore, this sample size of 60 serves as a pragmatic and methodologically sound approach. It is sufficiently large to evaluate our primary feasibility metrics and safety profiles, while providing exploratory signals regarding the cumulative opioid consumption to inform future research.

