To preserve the integrity of the initial randomization sequence while avoiding the imputation of an entire evaluation period for early dropouts, the primary efficacy analysis will be conducted adhering to a modified Intention-to-Treat (mITT) principle. This approach encompasses all randomized participants who received the allocated intervention and underwent at least one post-randomization clinical assessment. To handle potential missing longitudinal data resulting from early clinical discharge, severe postoperative complications, or protocol non-adherence, the analysis will rely on the inherent capacity of the GLMM to manage missing observations under the Missing at Random (MAR) assumption. Additionally, to account for data that may be Missing Not at Random (MNAR)—particularly due to asymmetric dropout rates driven by intervention-related adverse effects such as cybersickness—a sensitivity analysis utilizing Pattern-Mixture Models will be conducted to assess the robustness of the primary findings. Furthermore, a secondary per-protocol analysis will be performed for participants who completed a minimum of two therapeutic sessions per day to evaluate the intervention’s efficacy under optimal adherence conditions. A standard significance level of p < 0.05 will be established. Finally, the statistician performing the final data analysis will be blinded to the group allocation codes.

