Moreover, the implementation of this protocol relies on a stable technological infrastructure. As identified during pilot assessments, hospital wireless network blind spots can disrupt the delivery of streaming content, necessitating the use of pre-downloaded offline media as a mandatory contingency for the passive therapy arm. Parallel to these technological barriers, language can act as an immersion limiting factor. Since the primary interactive applications utilized, such as First Hand and Oculus First Contact, feature English interfaces and audio, non-fluent patients might experience a reduced sense of presence. The risk of cybersickness, although minimized by the careful selection of appropriate software, also remains a physiological factor that could lead to the premature cessation of sessions in highly susceptible individuals.

Because the protocol strategically focuses on a specific age group of 16 to 40 years to ensure technological familiarity, the results may not be directly generalizable to older populations, who might face completely different cognitive or physical challenges when interacting with VR technology. Ultimately, as a single center trial conducted within a highly specialized academic institution, the findings may have limited external validity when extrapolated to community hospitals with different resource constraints. Furthermore, the study design restricts the evaluation window to the acute perioperative phase, concluding on the fifth postoperative day or at hospital discharge. This timeframe inherently limits the ability to assess the long term impact of the VR intervention on the prevention of chronic postsurgical pain or prolonged opioid dependence.

Finally, as a proof-of-concept trial, this study has inherent statistical limitations. The pragmatic sample size of 20 patients per arm (N = 60 total) is prospectively established without a population-specific a priori power calculation. Consequently, while this sample size is mathematically adequate to detect large clinical effect sizes and provide initial estimates of variance, the study may be underpowered to identify small-to-moderate differences in cumulative opioid consumption or pain intensity. Therefore, the risk of a Type II error cannot be completely ruled out, and these findings should be interpreted as preliminary efficacy signals that require validation in future, fully powered definitive multicenter trials.

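### No primary contrast or gate is named for a three-arm trial tested at 0.05, what is primary varies between sections, and the claim that 20 per arm suffices for large effects has no calculation behind it

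*Protocol article*

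**What the plan says.** **Design and size.** Study design and randomization describes a "three-arm clinical trial design with a 1:1:1 allocation ratio". Sample size and study population states that "a pragmatic sample size of 20 patients per arm (total N = 60) is established" and that "a formal a priori power calculation for clinical efficacy is not performed".

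**Testing.** The Statistical analysis plan section assigns the primary outcome (opioid consumption as morphine equivalents per 24 h) and the repeated pain scores to generalized linear mixed models only, with surgical type as a covariate. It then says "A standard significance level of p < 0.05 will be established". It does not say whether that level applies to the overall arm effect, to one contrast or to each pair. Virtual reality interventions raises the comparison of the enriched arm (Group 1) with the passive arm (Group 2). Clinical endpoints and blinding speaks of intervention against control, without saying whether the two VR arms are pooled.

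**What is primary.** Background gives the primary objective as the "preliminary clinical efficacy of this multi-session VR protocol on cumulative opioid consumption and pain intensity". Sample size and study population says of the 60 patients: "It is sufficiently large to evaluate our primary feasibility metrics and safety profiles". It treats opioid consumption there as an exploratory signal. Clinical endpoints and blinding makes cumulative opioid consumption the primary endpoint and pain intensity a secondary outcome.

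**Adequacy.** Limitations states that "this sample size is mathematically adequate to detect large clinical effect sizes". It also concedes low power for small-to-moderate differences.

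**The concern.** A significance level controls error only once it is tied to a test. With three arms there are three pairs, and the article gives a reason to look at each kind of comparison. Without a named contrast or gate, whichever pair falls below 0.05 could be reported as the efficacy signal. The article intends such signals to guide definitive trials, so a false one has a cost.

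The adequacy sentence presents the sample size as sufficient on mathematical grounds, although the article says elsewhere that no such calculation was made. A reader planning the next trial could take a null pairwise result as evidence against a large effect when the comparison had only moderate power to find one.

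The shifting primary aim adds to this, because the level of 0.05 attaches to different things depending on the section read.

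**Working it through.** **Inputs.** Three arms, 1:1:1, 20 per arm, level 0.05 (all from the article). Assumed because the article does not say: two-sided tests; one approximately normal value per patient with equal variance; large meaning d = 0.8 for a pair or f = 0.40 for three groups.

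**The plan's own figure.** N = 60 agrees as a count: 3 × 20 = 60, and twenty blocks of three = 60. It cannot be reproduced as a power result, because no effect size, SD or power is given.

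**Family-wise error when no arm differs** (pooled variance, 60 − 3 = 57 df):
- The two-sided 5% critical t on 57 df is 2.002. Three ungated pairwise tests reject at least once when the studentized range for three means exceeds 2.002 × √2 = 2.832. That probability is 12.1% (simulation of 200,000 trials: 12.2%).
- Two ungated tests against control: 9.1% (simulation).
- Pairwise tests only after a significant 2-df test: 5.0% (simulation).

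**Pairwise power, 20 against 20** (noncentral t, 38 df). The noncentrality is d × √(20/2), which is 0.8 × 3.162 = 2.53 at d = 0.8.

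| d | Level 0.05 | Level 0.05/3 (Bonferroni) |
|---|---|---|
| 0.8 | 69% | 52% |
| 0.9 | 79% | 64% |
| 1.0 | 87% | 74% |
| 1.2 | 96% | 90% |

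The d detectable with 80% power is 0.91 at 0.05 and 1.06 with Bonferroni.

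**Dropout.** The article plans no allowance. Its eligibility text cites rates of up to 13% in other trials, and 20 × 0.87 = 17.4, so about 17 per arm. Power at d = 0.8 is then 62%, and the detectable d is 0.99.

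**Omnibus power.** The noncentrality is N × f² = 60 × 0.16 = 9.6 on 2 and 57 df, giving 78% power at f = 0.40. If one arm differs from the other two by 0.8 SD, f = 0.377 and power is 72%.

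**Covariate.** If surgical type explains a share R² of the variance, the effective d is 0.8/√(1 − R²). The article gives no R². Assumed values of 0.1, 0.2 and 0.3 give pairwise power of 74%, 79% and 84%.

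**Cost of a gate.** Suppose one VR arm differs from control by 0.8 SD and the other does not (pooled variance, 57 df, simulation):

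| Rule | Gate rejects | Effective arm found against control |
|---|---|---|
| No gate | not applicable | 70% |
| 2-df arm test first | 72% | 64% |
| Pooled VR against control first | 30% | 30% |

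The ungated 70% differs from the 69% above only because the variance is pooled over three arms.

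**The case against.** **The 12% is not a property of the plan.** A reader might infer that the trial will run at 12% family-wise error. The article does not support that. It never commits to three ungated pairwise tests, the arm term in the mixed model may be tested on 2 df, and a fuller analysis plan may settle the order of contrasts. This stands. The 12% is the highest of three cases for the primary endpoint.

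**The adequacy claim is not shown to be false.** A reader might infer that 20 per arm fails for large effects. That depends on reading large as 0.8 SD. The omnibus test comes close to 80% at f = 0.40, a useful covariate could bring a pair close to 80% at 0.8 SD, and from about 0.91 SD a pair has 80% without adjustment. This also stands. What remains is that the claim is called mathematical, defines no effect and has no calculation behind it.

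**Pain is not a second primary endpoint.** The Background wording might suggest two primaries and so a larger error rate. The endpoint and analysis sections both make opioid consumption primary and pain secondary, so no such inflation is claimed. The inconsistency in wording remains.

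**The cited meta-analytic effect is no benchmark.** The article declines to use earlier effect sizes for a power calculation, and that one concerns analgesic efficacy rather than opioid consumption.

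**The trial is a proof of concept.** It discloses the missing power calculation and the risk of a Type II error. This lowers the severity. But the caveat covers only small-to-moderate differences, leaves the claim about large effects in place and says nothing of Type I error. A fuller analysis plan could name a contrast, but it would not correct Limitations or align Background and the sample size section with the endpoint section.

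**Conclusion.** The concern holds in a conditional form.

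- **Multiplicity.** The article fixes a level but not the test that it governs. Family-wise error on the primary endpoint would be 5%, 9% or about 12%, depending on a choice that the article leaves open.
- **Adequacy.** The statement is unsupported. At an assumed 0.8 SD, pairwise power is 69% (52% with Bonferroni) before dropout. Reaching 80% takes about 0.91 SD (1.06 with Bonferroni). Adjustment for surgical type could improve this by an amount that the article does not give.
- **Primary aim.** Background, Sample size and study population, and Clinical endpoints and blinding give three different accounts. This is a contradiction within the article and does not depend on any assumption.

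The figures rest on two-sided tests, normal data with equal variances and one value per patient. The point should be corrected but does not threaten the trial, given its declared exploratory purpose.

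**What to change.** 1. State opioid consumption in morphine equivalents per 24 h as the sole primary endpoint, and bring Background and Sample size and study population into line with Clinical endpoints and blinding.
2. Test the 2-df arm effect in the mixed model at two-sided 0.05. Only if it rejects, test the three pairwise contrasts, each at 0.05. With three arms this holds the family-wise error at 5%: if all arms are equal the gate controls it, and otherwise at most one pairwise null can be true, which is tested at 0.05.
3. Replace the adequacy sentence in Limitations with the detectable pairwise effect at 80% power: about 0.91 SD with 20 per arm, or about 0.99 SD with 17.

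A pooled VR-against-control gate is not recommended as the lead test. It rejects only 30% of the time if one VR arm works at 0.8 SD and the other does not, and the article sets out to judge each VR strategy.

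The cost is wording, with no extra patients. The downside is a small loss of pairwise power, from about 70% to 64% at 0.8 SD when one arm differs.

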## Safety protocols and physical restrictions

To ensure the physical safety of patients recovering from highly invasive cardiothoracic procedures—who present with median sternotomies, chest tubes, and central venous catheters—strict safety protocols are implemented during all interventions. A trained healthcare professional remains continuously at the bedside for the entire duration of every VR session to supervise the patient, manage the hardware, and prevent any hazardous movements. Patients are comfortably positioned in their ICU beds, and upper limb movements are strictly monitored to adhere to standard sternal precautions, preventing excessive shoulder abduction or overextension.

Recognizing the varying physical demands of the software, the active VR arm employs a progressive interaction strategy. Patients are allowed to begin with passive observation or low-intensity applications (e.g., Oculus First Contact). As they demonstrate comfort and clinical stability, they may gradually advance to games requiring moderate arm movement (e.g., Fruit Ninja, Beat Saber), strictly within their pain-free range of motion. This stepwise approach maximizes patient adherence while ensuring physical safety. The preliminary pre-trial pilot phase of this study explicitly tested and validated this supervised, progressive methodology, confirming its clinical safety and operational feasibility without compromising surgical incisions or indwelling lines.

## Protocol validation

The validation of this protocol framework is based on a preliminary, pre-trial pilot phase conducted at the Heart Institute (InCor) with an initial sample of 3 patients, encompassing a total of 45 sessions. This preliminary phase was designed to ensure that the integration of Virtual Reality (VR) technology does not interfere with standard Intensive Care Unit (ICU) monitoring or clinical workflows. This strict preliminary evaluation of technical parameter settings and hardware feasibility aligns perfectly with recent methodological benchmarking for VR pilot designs in thoracic populations, as demonstrated by Cao et al. (2025) [10]. Preliminary technical tests confirmed that the Meta Quest headsets maintain optimal performance for the full duration of the 30 to 45 min sessions, without any instances of overheating or software crashes. Furthermore, during the pilot phase, hospital wireless network blind spots were identified, which initially hindered the functionality of the passive therapy arm that relied heavily on YouTube VR content. To successfully circumvent this technical barrier, high-quality 360-degree videos were downloaded and stored directly on the internal memory of the headsets, ensuring uninterrupted passive therapy delivery even in locations without internet access.

In addition to technical stability, the hygiene protocol using 70 percent isopropyl alcohol and neutral soap was rigorously tested for its impact on equipment durability. Results from the pilot evaluations showed no degradation of the lenses or facial pads, thus validating the long term feasibility of shared device use within a highly regulated hospital setting.

Consequently, patient safety was quantitatively validated throughout the entire pilot period by continuously monitoring vital signs, including heart rate, mean arterial pressure, oxygen saturation, and respiratory rate, alongside tracking signs of cybersickness. In these preliminary assessments, patients within the targeted age group of 16 to 40 years reported high levels of comfort and ease of use with the hand tracking features in the First Hand and Oculus First Contact applications. Across the 45 executed sessions, the incidence of adverse events was limited to a single report of mild dizziness. While this represents an occurrence rate of 33.3% at the patient level (1 out of 3 patients), when analyzed by total therapeutic exposure, the adverse event occurred in only 1 out of the 45 sessions (a 2.2% per-session rate). Although this preliminary sample is too small to draw definitive conclusions regarding overall clinical safety, these pilot results confirmed the initial technical feasibility and general tolerability of the repeated-exposure protocol, allowing the main trial to proceed.

Moreover, the adherence rate was formally assessed, demonstrating that all the participants were able to successfully complete at least two of the three daily sessions, thereby meeting the minimum threshold established for inclusion in the final data analysis.

Finally, the data collection infrastructure was validated through a mock entry process using the REDCap platform. This procedure ensured that all clinical variables, particularly the Visual Analogue Scale (VAS) scores and precise opioid dosages extracted from patient-controlled analgesia (PCA) pumps, are accurately captured, synchronized, and ready for subsequent statistical analysis.

## Limitations

A primary limitation of this protocol is the inability to perform a double-blind study due to the nature of the intervention, as both the participants and the research team are inherently aware of the use of Virtual Reality (VR) headsets. Consequently, this lack of blinding may introduce a performance bias in the subjective reporting of pain levels through the Visual Analogue Scale (VAS) and in the evaluation of patient satisfaction via the PSQ 18 questionnaire. Additionally, patients allocated to the standard care control group might experience resentful demoralization. Knowing they are excluded from the novel technological intervention could negatively influence their subjective psychological state and artificially lower their satisfaction scores.

In addition, a notable limitation inherent to this study design is the presence of attention and expectancy biases. Patients allocated to the VR intervention arms inherently receive more direct, continuous attention from the research team during the setup and supervision of the sessions compared to the standard care control group. This discrepancy in social interaction, combined with the novelty effect of using an immersive technological device, may generate a positive expectancy or placebo effect that independently contributes to pain reduction and anxiety relief. While the use of an objective primary endpoint—cumulative opioid consumption, rigorously calculated by tracking both automated PCA pump logs and electronic medical records (encompassing oral and intermittent intravenous doses)—helps mitigate the subjectivity of self-reported pain scores (VAS), the psychological impact of receiving specialized, dedicated attention cannot be entirely isolated from the specific analgesic effects of the VR therapy itself.

In addition, environmental factors in the Intensive Care Unit, such as excessive noise, frequent clinical interruptions, or the presence of multiple invasive lines and chest tubes, may also severely limit the degree of immersion achieved by the patient.

Moreover, the implementation of this protocol relies on a stable technological infrastructure. As identified during pilot assessments, hospital wireless network blind spots can disrupt the delivery of streaming content, necessitating the use of pre-downloaded offline media as a mandatory contingency for the passive therapy arm. Parallel to these technological barriers, language can act as an immersion limiting factor. Since the primary interactive applications utilized, such as First Hand and Oculus First Contact, feature English interfaces and audio, non-fluent patients might experience a reduced sense of presence. The risk of cybersickness, although minimized by the careful selection of appropriate software, also remains a physiological factor that could lead to the premature cessation of sessions in highly susceptible individuals.

Because the protocol strategically focuses on a specific age group of 16 to 40 years to ensure technological familiarity, the results may not be directly generalizable to older populations, who might face completely different cognitive or physical challenges when interacting with VR technology. Ultimately, as a single center trial conducted within a highly specialized academic institution, the findings may have limited external validity when extrapolated to community hospitals with different resource constraints. Furthermore, the study design restricts the evaluation window to the acute perioperative phase, concluding on the fifth postoperative day or at hospital discharge. This timeframe inherently limits the ability to assess the long term impact of the VR intervention on the prevention of chronic postsurgical pain or prolonged opioid dependence.

Finally, as a proof-of-concept trial, this study has inherent statistical limitations. The pragmatic sample size of 20 patients per arm (N = 60 total) is prospectively established without a population-specific a priori power calculation. Consequently, while this sample size is mathematically adequate to detect large clinical effect sizes and provide initial estimates of variance, the study may be underpowered to identify small-to-moderate differences in cumulative opioid consumption or pain intensity. Therefore, the risk of a Type II error cannot be completely ruled out, and these findings should be interpreted as preliminary efficacy signals that require validation in future, fully powered definitive multicenter trials.

